### Organization

Oslo University Hospital is the Sponsor, i.e. the main responsible party for this study. Initial study planning was conducted in collaboration with St Olav’s Hospital, Trondheim, particularly related to setting up the Trial Office and preparing the adaptation, installation, and functional aspects of Eir and in the development of the PCCPs.

The local principal investigators and study nurses at the participating hospitals are responsible for patient inclusion and registration of clinical data in the e-CRF every 2 months. The Trial Office is located at St Olav’s Hospital, Trondheim, with study personnel being responsible for the overall data management and study administration. This includes administration of the e-CRFs, sending out and scanning the paper questionnaires to patients and caregivers, regular monitoring of data quality, and preparation of the final data files.

Patients included in the study are covered by the Patient Injuries Act. No particular insurance applies to relatives. Study participation is not likely to cause any harm to participants, be it patients or caregivers. Study results will be published in peer-reviewed journals. Authorship is based upon the Vancouver rules. All manuscripts will be prepared by the researchers.

## Trial status

Inclusion of patients and caregivers is ongoing. Recruitment started in March 2017. It took longer than anticipated to finish the comprehensive educational program at the intervention sites. As completion of this program was requested before the start of patient inclusion, it became evident that a prolongation of the study timeline was necessary. This has been updated in ClinTrials.gov and was approved by the Ethical Committee South East Norway as a study amendment in November 2019. The final date for study recruitment is 31 December 2020, or before if 680 patients have been included, to secure that the power requirements are met. The final date for patient follow-up is 31 December 2021, or before if the last included patient has been followed for 1 year or until death. Caregivers will be assessed at 6 and 12 months after the patient is dead, if they consent to continue in the study. Thus, caregiver follow-up will continue in 2022.

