## Background

Major concerns in oncology today are the rapidly increasing complexity of treatment, the steadily augmenting number of treatment lines that are administered, and new agents that increases the demand for anticancer treatment at end-of-life (EoL). Coupled with this is the increasing use of advanced imaging, i.e. computed tomography (CT) and positron emission tomography (PET) scans and magnetic resonance imaging (MRI). About one-third of the cost of cancer care is spent during the patient’s last year of life [1], and costs are expected to escalate rapidly, which threatens the sustainability of the present services [2, 3].

One article examined the rationale for discontinuation of chemotherapy for metastatic non-small-cell lung cancer (NSCLC) and identified a huge variability in these processes, unrelated to time of death [4], as addressed by others [5–7]. This is in spite of patients, families, and oncologists uniformly recognizing the administration of chemotherapy near death as aggressive and as an indicator of poor EoL care [8].

The American Society of Oncology (ASCO) has defined discontinuation of chemotherapy given with a life-prolonging intent in the last 2 weeks of life as a benchmark for improving clinical practice [9]. It is difficult to decide the optimal chemotherapy intensity during the last periods of life at an individual patient level. For example, if the treatment of choice in some patients with chemosensitive solid tumors is a therapy with modest side effects, a high response rate, and good symptom relief, this may be appropriate even if the life expectancy is < 3 months. However, a French registry-based study in > 279,000 patients found no clear pattern between the expected chemosensitivity of different solid cancers and the administration of chemotherapy at EoL [6].

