### The structured educational program

The aims of the educational program are to provide the participants—i.e. oncologists, doctors under specialization, PC physicians and residents—with sufficient competence, theoretical knowledge, understanding, and practical skills to make a complete integration of oncological care and PC in the PCCPs. The content of the program is specifically selected as they represent transitions in a disease and treatment trajectory, e.g. in relation to discontinuation of treatment and disease progression, and that are often perceived as difficult by clinicians, such as communication of prognosis and breaking bad news. Thus, the content of the lectures correspond with the organization of care and the specific content at each step of the PCCSs. Hence, the program is to be completed before patient inclusion in the PALLiON study, with a mandatory confirmation that it has been completed.

The educational program takes place at each of the six intervention hospitals. It consists of classroom lectures, Internet teaching videos, group work, and 1 day with communication skills training focusing on specific communication tasks related to integration of oncology and PC. The first of the eight lectures is a thorough introduction lecture presenting the scientific basis, organization, methods, and objectives of the PALLiON study. The following seven focus on central issues related to palliative treatment. They have an overall duration of 3 h, use the PowerPoint format, and are taped with voice-over to make them available in the e-learning program (see below). All lectures are given by experienced physicians who are specialists in oncology and/or PC and with long-standing clinical experience. The content is based on evidence-based treatment guidelines on chemotherapy and radiotherapy endorsed by the ASCO [66] and the American Society for Radiation Oncology [67], symptom assessment, and relevant literature related to each subject. The following areas are covered: (1) PALLiON—care pathways and integration of PC and oncology; (2) the educational program—objectives, structure, content, short info about Eir; (3) using Eir in clinical practice, symptom assessment; (4) prognostication, prognostic tools; (5) palliative radiotherapy; (6) palliative chemotherapy; and (7) EoL care.

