The e-learning program follows the structure of the one at the Faculty of Medicine at the University of Oslo and has an overall duration of 3 h. Four videos are used, in which a young patient with breast cancer is followed. An experienced nurse plays the patient while an experienced oncologist and an experienced PC physician feature the consulting physicians. The first video starts when the patient comes to the oncologist after having completed third-line chemotherapy a while ago. She is then followed towards death, with the films covering: prognostic information; treatment decisions, e.g. cessation of therapy; introduction of PC; and talking about death and dying. The videos are supplemented with exercises developed to reflect upon the contents of the films, learning objectives, presentations of specific communication skills, and references to relevant literature, intended for group or individual work at each intervention site.

The practical communication training is divided into two areas: (1) skills training; and (2) hands-on guidance. The first consists of local courses for small groups at the participating sites, focusing on specific communication challenges such as starting a discussion of prognosis and treatment intention, elucidating the patient’s preferences and provision of relevant information to patients facing termination of anticancer treatment and EoL. These are led by two experienced psychologists from the PALLiON education team and lasts for 1 full day. The hands-on guidance takes place after skills training. A local coach attends one consultation as an observing participant and gives the oncologist or PC physician feedback afterwards.

The structured educational program will be completed at all sites before patient inclusion and starts in the fall 2016. All lectures and instruction videos are available at the restricted access part of the PALLiON website and all participants in the intervention arm are encouraged to use this material for continuous discussions and updates. Access for participants in the control arm will be provided after study closure.

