##### Statistics

The design makes it possible to evaluate the effect of an early integration of oncology and PC at the institutional and patient levels across intervention and control arms, by comparing the use of chemotherapy in the last 3 months of life.

Analyses on the primary outcome will be performed when there are 300 patients in each arm with data on chemotherapy use in the last 3 months of life, which is the basis for the power estimation. Standard descriptive statistics will be used for background variables. Further, data will be analyzed by the intention-to-treat approach; mixed effect regression models will be used to analyze both primary and secondary endpoints in order to account for clustering. Logistic and linear regression models will be used respectively for binary and continuous outcomes and all models will be adjusted for potentially relevant baseline covariates at patient level, i.e. sex, age, diagnosis, performance status score, and baseline symptom scores. The analysis of the main outcome will also be adjusted by size of the catchment areas, which is the randomization stratification factor.

Survival analysis methods, i.e. Kaplan–Meier curves and Cox proportional hazards models with shared frailty terms to account for clustering and Kaplan–Meier curves, will be employed in order to model time to death. Sensitivity analyses to different methods will be applied to handle missing data in the secondary PROs: complete case analysis and multiple imputations. This also applies to patient- and caregiver-reported outcomes. Paper forms will be used to collect medical data and PROs for comparisons across arms.

Further, a potential effect of the intervention at each of the centers in the intervention arm may be evaluated at a later stage as an explorative outcome by comparing post-intervention data with historical data, e.g. on use of chemotherapy and number of readmissions/emergency admissions in the very last stages of life as appropriate.

The CONSORT recommendations for reporting RCTs will be followed. The CONSORT recommendations for reporting C-RCTs will be followed. IBM SPSS Statistics for Windows, version 25.0 (IBM Corp., Armonk, NY, USA) and STATA (Stata Corp. LCC, College Station, TX, USA) will be used.

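### Only intervention hospitals had to complete training before enrolling, and it overran; enrolment periods may therefore differ by arm, and inclusion date is not among the listed covariates

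*Protocol article*

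**What the plan says.** **Training falls on one arm.** The structured educational program section states: "The educational program takes place at each of the six intervention hospitals". It also states that "the program is to be completed before patient inclusion in the PALLiON study, with a mandatory confirmation that it has been completed". For control staff: "Access for participants in the control arm will be provided after study closure". The same section puts the programme's start in autumn 2016.

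**It overran.** Under Trial status: "It took longer than anticipated to finish the comprehensive educational program at the intervention sites". Because completion was required before inclusion, "it became evident that a prolongation of the study timeline was necessary". The only start date given is for the trial as a whole: "Recruitment started in March 2017". Recruitment closes on 31 December 2020, or earlier if 680 patients have been included.

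**Practice is described as changing.** The Background names as concerns "the steadily augmenting number of treatment lines that are administered, and new agents that increases the demand for anticancer treatment at end-of-life (EoL". No yearly rate is given, and no trend for the primary endpoint.

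**Adjustment.** Under Statistics, "all models will be adjusted for potentially relevant baseline covariates at patient level, i.e. sex, age, diagnosis, performance status score, and baseline symptom scores". Catchment-area size is added for the main outcome. The Sample size section refers the reader to the statistics section for the complete set of proposed covariates. Inclusion date is not in it, although the section on the EAPC basic dataset lists date of consent among the items on the patient form.

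**The concern.** A parallel trial is protected against changes in practice over time because both arms enrol during the same months. Here one arm has a compulsory step before its first patient and the other does not. That step took long enough to move the end date of the whole study.

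If control hospitals enrolled while some intervention hospitals were still in training, intervention patients would on average have been included later. Table 3 fixes a planned number of patients per hospital (85, 50 or 35), so a hospital that opens late may also finish late, and an initial lag need not even out. Part of the difference in chemotherapy use in the last 3 months of life would then be a difference between calendar periods. The exploratory survival and cost comparisons would be exposed in the same way.

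**Working it through.** **1. What the article settles and what it leaves open**

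| Question | Answer in the article |
|---|---|
| Is training required before enrolment? | Yes, in the intervention arm only |
| Did it overrun? | Yes, and the study timeline was prolonged |
| Length of recruitment window | March 2017 to December 2020, at most 46 months |
| Opening dates by hospital or arm | Not given |
| Were control hospitals held back meanwhile? | Not stated |
| Yearly trend in the primary endpoint | Not given |
| Inclusion date among the covariates | No |

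**2. Reproducing the design figure**

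Inputs from the Sample size section: 45% against 20%, two-sided 5%, 80% power, 12 hospitals (6 per arm), ICC 0.08, r_adj 0.1, 300 evaluable patients per arm. Hospitals are taken as equal, so m = 300/6 = 50.

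SE² = [p_C(1 − p_C) + p_I(1 − p_I)] × [1 + (m − 1) × ICC] × (1 − r_adj²) / 300

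SE² = (0.2475 + 0.1600) × 4.92 × 0.99 / 300 = 0.006616, so SE = 0.0813.

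Power = Φ(difference/SE − t(0.975; 10 df)) = Φ(0.25/0.0813 − 2.228) = Φ(0.845) = 80.1%.

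The same formula gives 18 of the 20 cells of Table 2 exactly. The other two differ by one patient per cluster (318 against 312, and 636 against 630). The sample size is not in question; the formula serves only to scale the illustration.

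**3. Illustration of a bias toward the null**

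Bias = yearly change in the rate × gap between the arms in mean inclusion date. Both factors are assumptions: 1 to 4 points per year and 0.5 to 1.5 years. The product runs from 1 × 0.5 = 0.5 to 4 × 1.5 = 6 points. The case shown is rising use with the intervention arm enrolled later, so the intervention rate moves up from 20% while control stays at 45%.

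| Bias (points) | One way to reach it | Apparent difference | SE | Power |
|---|---|---|---|---|
| 0 | no gap or no trend | 25 | 0.0813 | 80% |
| 0.5 | 1/year × 0.5 years | 24.5 | 0.0816 | 78% |
| 1 | 1/year × 1 year | 24 | 0.0819 | 76% |
| 2 | 4/year × 0.5 years | 23 | 0.0825 | 71% |
| 3 | 3/year × 1 year | 22 | 0.0830 | 66% |
| 5 | 4/year × 1.25 years | 20 | 0.0840 | 56% |
| 6 | 4/year × 1.5 years | 19 | 0.0845 | 51% |

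Worked line for 3 points: SE² = (0.2475 + 0.23 × 0.77) × 4.92 × 0.99 / 300 = 0.006894; 0.22/0.0830 − 2.228 = 0.42; Φ(0.42) = 66%.

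**4. The other direction**

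If chemotherapy use near death were falling, later enrolment in the intervention arm would exaggerate the benefit: with a 3-point shift, a true 25 would read as 28. The Background points to rising demand. The article also cites an updated guideline on integrating palliative care and a commission paper favouring care pathways, which could push use down. The sign is therefore not determined.

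**The case against.** The strongest reply is that the decisive fact is absent. A reader might infer that intervention patients were enrolled later and that arm and calendar time are confounded. The article does not say so. It gives one recruitment start for the trial, the programme was due to begin before that date, and the delay is described as prolonging the whole study. Control hospitals may have been held back. This objection stands, and it limits the point to a risk.

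Second, the trend is weakly evidenced. The Background passage is qualitative and does not concern chemotherapy in the last 3 months specifically. The article also says that oncology and palliative care remain distinctly separate in Norway, which does not suggest a fast-moving baseline. This stands too. A statement that part of the observed effect will be a period effect goes beyond the text. Against a standard error of about 8.1 points, the lower end of the assumed range is negligible (0.5/8.1 = 0.06 SE). The upper end (6/8.1 = 0.74 SE) needs both assumptions at their maximum.

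Third, an analysis plan that is not shown may already handle enrolment period, and staggered opening of sites is ordinary in multicentre trials. This stands in part. It cannot be said that no analysis of the trial adjusts for date. But the article presents its covariates as the complete proposed set, so the point concerns a stated list. The staggering here also comes from a requirement placed on one arm, not from chance variation between sites.

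Fourth, if date and arm are strongly correlated, adjustment costs precision in a trial with only 12 clusters. That is true and belongs among the costs.

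**Conclusion.** The point holds as a risk that the article neither excludes nor guards against. Three elements are documented: a precondition for enrolment in one arm only, an overrun that lengthened the study, and a stated covariate list without inclusion date. Different enrolment periods by arm are a plausible consequence, not a reported fact, and a biased result is not shown.

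No actual size can be derived, because the article gives neither the gap nor the trend. Under the assumed ranges the bias would be 0.5 to 6 points on the planned 25. If toward the null, power at the design cell would fall from 80% to between about 78% and 51%; a 3-point bias gives 66%. These figures assume equal clusters of 50 and the Table 2 formula. A trend in the other direction would inflate the apparent benefit. The change is inexpensive and worth making; the design itself is not called into question.

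**What to change.** 1. Add date of inclusion, taken from the date of consent, as a patient-level covariate in the primary model, or at the least in a prespecified sensitivity analysis of it. Fix its form in advance, for example half-year periods or a linear plus quadratic term. Do the same in the survival and cost models.
2. Report the date of first enrolment for each hospital and the distribution of inclusion dates by arm. If these overlap well, the concern is largely answered.
3. Prespecify a sensitivity analysis restricted to patients enrolled after the last intervention hospital opened. This removes imbalance at the start of recruitment only; any difference in when the arms finished is left to the covariate.

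**Cost.** Wording in the analysis plan and no new data collection. The covariate takes one or a few degrees of freedom at patient level. Some precision is lost if date and arm are correlated, and the restricted analysis uses a smaller sample.

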## Data Availability

The datasets generated and/or analyzed during the current study are available from the corresponding author on reasonable request.

## Abbreviations

BPI: Brief Pain Inventory
CONSORT: Consolidated Standards of Reporting Trials
C-RCT: Cluster-randomized controlled trial
CTCAE: Common Terminology Criteria for Adverse Events
CV: Coefficient of variation
EAPC: European Association for Palliative Care
e-CRF: Electronic case report form
EoL: End-of-life
EORTC QLQ-INFO25: European Organisation of Research and Treatment of Cancer Quality Questionnaire-Information
EORTC: European Organisation for Research and Treatment of Cancer
EPA: European Pathway Association
e-PROM: Electronic patient reported outcome measure
ESAS: Edmonton Symptom Assessment System
F-36: Short Form-36
FAMCARE: Family Satisfaction with End-of-Life Care
FDA: Food and Drug Administration
GAD: General anxiety disorder
GT: Gamma-glutamyltransferase
HCP: Healthcare professionals
ICC: Intra-cluster correlation coefficient
KPS: Karnofsky Performance Status
LD: Lactate-dehydrogenase
NRS: Numerical rating scale
NSCLC: Non–small cell lung cancer
NTNU: Norwegian University of Science and Technology
PC: Palliative care
PCCP: Patient-centered care pathway
PHQ-9: Patient Health Questionnaire-9
PRO: Patient-reported outcome
PROM: Patient-reported outcome measure
QLQ-C15-PAL: European Organisation of Research and Treatment of Cancer Quality Of Life Questionnaire Core 15 Palliative
QoL: Quality of life
RCT: Randomized controlled trial
REC: Regional Committee for Medical and Health Research Ethics
RECIST: Response Evaluation Criteria In Solid Tumors
SCO: American Society of Oncology
SCP: Standardized care pathway
SGA: Subjective Global Assessment for nutritional status
SPIRIT: Standard Protocol Items
WHO: World Health Organization
